## Abstract

**Background:**

Advances in autologous hematopoietic stem cell transplantation (HSCT) and supportive care have led to marked improvements in survival for patients with multiple myeloma. Despite these improvements, patients with multiple myeloma remain at high risk of physical dysfunction and frailty due to HSCT and its associated exposures. Although traditional supervised exercise programs can improve frailty in cancer patients and survivors, rehabilitation facilities are typically far from a patient’s residence, are offered on fixed days/hours, contain uniform activities for everyone, and carry a higher risk of contact cross-infection due to immunosuppression, which can be barriers to exercise participation. Innovative personalized interventions are needed to overcome the limitations of traditional exercise interventions. The purpose of this study is to determine the efficacy and sustainability of a telehealth exercise intervention on physical function and frailty in patients with multiple myeloma treated with HSCT.

**Methods:**

This randomized controlled trial will assess the efficacy of an 8-week telehealth exercise intervention in 60 patients with multiple myeloma who underwent autologous HSCT (30–180 days post-transplant) and are pre-frail or frail. There will be 30 intervention participants and 30 delayed controls. We will administer remote baseline assessments (week 0), followed by an 8-week telehealth intervention (week 1–8), post assessment (week 9), and an additional follow-up assessment (week 17). Our primary endpoint will be improved physical function, as assessed by the Short Physical Performance Battery test. Our secondary endpoint will be a decrease in frailty characteristics such as gait speed, strength, and fatigue. We will also evaluate the sustainability of improved physical function and frailty at week 17. Participants randomized to the intervention group will perform at least 90 min of exercise per week throughout the 8 weeks.

**Discussion:**

This study will help optimize the delivery of safe, low-cost, and scalable telehealth exercise interventions to improve health outcomes in patients with multiple myeloma, an understudied population at high risk for physical dysfunction and frailty. Our study may provide the foundation for sustainable telehealth exercise interventions to improve physical function and frailty for other hematologic cancer patients (e.g., acute leukemia, lymphoma) as well as any other cancer population of interest.

**Trial registration:**

ClinicalTrials.govNCT05142371. This study was retrospectively registered on December 2nd, 2021, and is currently open to accrual.

**Supplementary Information:**

The online version contains supplementary material available at 10.1186/s13063-022-06848-y.

## Background

Advances in autologous hematopoietic stem cell transplantation (HSCT) and supportive care have led to marked improvements in survival for patients with multiple myeloma [1]. In fact, multiple myeloma is the most common indication for autologous HSCT, with an estimated 67% of patients with multiple myeloma comprising the total HSCT in the USA annually [2]. Despite these improvements, patients with multiple myeloma remain at high risk of physical dysfunction and frailty due to HSCT [3], and its associated exposures [4]. Frailty can be defined as having three or more of the following: clinically underweight, exhaustion, low energy expenditure, slow gait speed, and weak strength [3, 5, 6]. It is estimated that two thirds of patients with multiple myeloma have aging-related health conditions such as frailty [7]. The International Myeloma Working Group reported that frail patients with multiple myeloma have the lowest survival rate after 3 years (57% vs 84%) as well as the highest treatment discontinuation (31.2% vs 16.5%) compared to non-frail patients [8]. Additionally, frailty is associated with a 2.7-fold higher risk of mortality in HSCT survivors when compared with those who are not frail [3], which further emphasizes the need for innovative prevention strategies to mitigate these modifiable complication risks after autologous HSCT.

Exercise interventions for hematological cancer survivors have been implemented to reduce treatment-related side effects and counteract physical inactivity. Several studies have examined the effects of exercise before [9–11], during [12, 13], or after [14–17] HSCT. However, studies have not utilized a fully remote telehealth exercise approach on physical function and frailty in these patients. Moreover, previous studies have not focused on patients at risk for developing frailty to show the benefits of participating in an exercise intervention in those at highest risk for adverse health outcomes. This unspecified selection of participants may have led to an underestimation of exercise effects, which has hindered the development of optimal exercise interventions for these patients.

Exercise is one of the most effective strategies to improve physical function and frailty in patients with chronic health conditions including heart failure [18], stroke [19], and cancer [20]. Unfortunately, exercise intervention studies presently face substantial challenges in implementation due to the COVID-19 pandemic [21], which has resulted in the closures of exercise facilities due to the need to maintain appropriate social distancing [22]. One potential exercise approach that does not require in-person attendance and can be accessed anytime and anywhere is a telehealth exercise intervention. A telehealth exercise intervention is an effective alternative model of home-based rehabilitation that can possibly produce higher compliance rates and similar efficacy when compared with hospital-based programs [23]. Studies in patients with coronary artery disease [24], and heart failure [25] have shown that a telehealth exercise intervention is equivalent to traditional cardiac rehabilitation in achieving functional improvement, managing risk factors (blood pressure, lipid profile, and body mass index), and improving quality of life, without serious adverse events. Despite strong evidence supporting the safety and effectiveness of home-based cardiac rehabilitation [26, 27], to our knowledge, no studies have used fully remote exercise interventions to prevent the risk of physical dysfunction and frailty in patients with multiple myeloma.

Therefore, the purpose of this trial is to evaluate a supervised telehealth exercise intervention (at least 30 min/session × 3 days/week for 8 weeks) that is aimed at improving physical function and frailty in patients with multiple myeloma soon after transplant (30–180 days post-transplant). Our primary outcome is physical function, as assessed by the Short Physical Performance Battery test. Our secondary endpoints are frailty characteristics such as gait speed, strength, and fatigue. We will also evaluate the sustainability of improved physical function and frailty at week 17. We will use an innovative telehealth exercise platform (Moterum Technologies, Salt Lake City, USA) which enables remote exercise interventions (e.g., home-based) that are accessible through digital platforms (e.g., video conferencing on smartphones or tablets) and customizable for users to properly address the individual needs of each participant. We hypothesize that the intervention will improve the Short Physical Performance Battery (SPPB) test and 5-scale frailty index, as objectively ascertained using Bluetooth-enabled biosensors and patient-reported questionnaires, respectively.

## Methods/design

A single-center, investigator-blinded randomized, parallel-group, superiority study was conducted to demonstrate the efficacy of a telehealth exercise intervention on physical function and frailty in patients with multiple myeloma who received HSCT at City of Hope (COH). Figure 1 depicts the flow of the study. We will conduct an 8-week telehealth intervention that will include baseline (week 0) and post-intervention measures (week 9, week 17) on physical function and frailty measures. We will randomize 60 pre-frail or frail patients with multiple myeloma (1:1) to either the 8-week telehealth exercise intervention group (*n*=30) or the delayed control group (*n*=30). All study procedures, including screening and enrollment, will be performed using a telehealth-based approach and will not require participants to be assessed at a clinical center.

**Fig. 1 Fig1:**
[figure not shown]
Study flow chart. Participants are randomized into either the telehealth exercise group or the delayed control group for 16 weeks. Participants in the delayed control group are offered the same exercise program after the week 17 assessment

### Eligibility

Eligibility requirements include (1) diagnosed with multiple myeloma; (2) ≥18 years of age; (3) self-reported as pre-frail or frail (i.e., Fried criteria: clinically underweight, exhibiting exhaustion, low energy expenditure, slow walking speed, and muscle weakness), with the presence of 2/5 indices classified as pre-frail and ≥3/5 indices classified as frail; (4) within 30 to 180 days post-HSCT prior to registration; (5) physically able and willing to complete all study procedures; and (6) English-speaking. Patients will be excluded if they (1) have clinically significant/active cardiovascular disease (e.g., unstable angina, uncontrolled arrhythmia, etc.); (2) have contraindications to exercise (acute infectious disease or unstable bone lesions); (3) currently recovering from a recent injury or have been physically injured in the past 6 months, in which participation in rigorous exercise may not be appropriate; (4) self-reported ongoing participation of exercise over 60 min per week; and (5) are female patients who are pregnant or planning to become pregnant. As acknowledged in the manuscript, patients who are frail generally have worse outcomes than those who are not, including worse survival and higher treatment discontinuation rates. However, the optimal timing for interventions to reverse frailty is not known. We have elected to include individuals who are pre-frail, as they may represent an optimal phenotype to target for the long-term sustainability of the intervention, prior to the onset of potentially irreversible physical functional decline. We anticipate that the randomized design of the trial will allow for a balanced allocation of pre-frail and frail study participants between the two arms.

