### Recruitment/randomization

If potentially eligible patients are interested in the study, a trained clinical research assistant will confer with the patients in detail about the additional study inclusion/exclusion criteria by phone. Once patients have been deemed eligible for participation, they will complete an informed consent via a web-based consent form (DocuSign™) prior to performing any further testing (see supplementary file). Participants will be randomly assigned to the telehealth exercise intervention group (*n*=30) or delayed control group (*n*=30). Randomization will be performed following physician’s clearance to participate in exercise and baseline outcome assessment using a computer-generated permuted block randomization. An independent biostatistician will be responsible for randomization and study investigators will be blinded to the randomization. Unblinding may need to occur in the case of a medical emergency or a serious medical adverse event study-directed exercise. Unblinding will be done in consultation with the study physician, and the institutional Data Safety Monitoring Board will be notified according to institutional standard operating procedures.

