### Power calculations

This study is powered to detect a difference in physical function between the two groups after the 8-week intervention. Assuming that a type 1 error = 0.05, data is collected at two time points, there is 20% attrition from baseline to week 9, and there is a correlation of ≥ 0.8 for within-person measurements between time, 60 patients (30 per group) at baseline will achieve 80% power to detect an effect size of at least 0.40 at week 9. A previous study of an 8-week exercise intervention in cancer survivors showed that baseline physical function was 6.7, SD=2.7, with a correlation of 0.9 between baseline and post-intervention [28]. By applying these values to patients with multiple myeloma who underwent HSCT, the present study will be able to show a difference of at least 1 in function score between the treatment groups post-intervention. A 1-unit decrease in the physical function score has been associated with a 12% increase in all-cause mortality in cancer survivors [29], and represents a clinically meaningful difference. The attrition rate in our previous study was 0% [28]. Nevertheless, we conservatively assumed a higher attrition rate of 20% and a lower correlation of 0.70; thus, 60 subjects at baseline (30 telehealth exercise intervention, 30 delayed controls) should provide even greater power since our preliminary study had a higher correlation as well as an attrition of less than 10%.

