### Statistical analysis

We will generate descriptive statistics for participants’ demographics, lifestyle behaviors (physical activity, tobacco use), family history of chronic disease, history of other comorbidities (e.g., hypertension, diabetes, dyslipidemia, thyroid disease), and cancer treatment-related exposures. We will assess participation bias by comparing demographics (age, gender, race/ethnicity) and treatment-related exposures among participants and non-participants. Although the number of adverse events is not the major outcome of the study, we will report any adverse events during the study intervention period. We will use a two-sided type I error=0.05. An intention-to-treat analysis will be done by including all randomized participants. We will also conduct another analysis by excluding participants that demonstrate <70% compliance rates within the telehealth exercise sessions completed (17/24). *Hypothesis 1*: The intervention will improve the SPPB test, as objectively measured using Bluetooth-enabled biosensors. We will assess changes in physical function from baseline to week 9 by using the Generalized Estimation Equation (GEE) model with an indicator variable of time, accounting for within-person correlations in measurements. Treatment by time interaction will be included in GEE and its significance tested to assess treatment effects. Body mass index, age, and race will be determined through medical records and included in GEE as a priori covariates for adjustment. Changes in physical function measures from baseline to week 9 will also be examined by a paired *t*-test (within the treatment group). A 2-sided significance level of *p*<0.05 will be used. *Hypothesis 2*: The intervention will improve a 5-scale frailty index, as measured by patient-reported questionnaires. We will assess group differences in changes in the proportion of participants who are of pre-frail or frail from baseline to week 9 using the GEE approach for proportions, accounting for correlation between measurements. As in hypothesis 1, we will include the same covariates for adjustment in the analysis. *Hypothesis 3*: Intervention-related improvements in physical function and frailty will be sustained at week 17. We will examine the long-term effects of the telehealth exercise intervention by fitting GEE models for the outcomes at weeks 9 and 17. The model will include the treatment main effect (to allow for group differences at week 17), time, and the treatment group by time interaction. Contrasts will be used to test if the group difference at week 17 equals that at week 9. As in hypothesis 1, we will include the same covariates for adjustment. Additionally, between-group differences in outcome values at week 17 will be computed, along with 95% confidence intervals, and compared to the differences at week 9. Linear mixed-effects modeling will be used to evaluate the effect of interventions over time on the primary and key secondary outcomes. The models incorporate subject-specific random effects to account for within-subject correlation due to repeated measures. Group averages, as well as subject-specific intercepts and slopes, will be estimated to capture potential variations in the baseline values and slopes among individuals. Linear mixed-effects models accommodate missing data due to dropout, such that all randomized participants can be included. We will compare participants who complete the study with those who do not and identify potential factors that are associated with dropout. An interim analysis is not currently planned for this study.

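### Days since transplant is known at entry but is not a prespecified covariate; adding it in the right form could buy some precision

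*Protocol article*

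**What the plan says.** The Eligibility section of the Protocol article sets the entry window as "within 30 to 180 days post-HSCT prior to registration". The Statistical analysis section states the adjustment set for the SPPB model: "Body mass index, age, and race will be determined through medical records and included in GEE as a priori covariates for adjustment". The same set is carried over to the frailty analysis (hypothesis 2) and the week-17 analysis (hypothesis 3). Days since transplant is not in it.

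The primary test is the interaction from baseline to week 9: "Treatment by time interaction will be included in GEE and its significance tested to assess treatment effects". Allocation is made "using a computer-generated permuted block randomization", and the article names no stratification factor. The article does not list days since transplant as an analysis variable. However, the value has to be established for every participant to apply the entry criterion, and the Prescreening/screening section describes a transplant database at the centre.

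**The concern.** The Background attributes the patients' physical dysfunction and frailty to the transplant and its associated exposures. If that is so, someone enrolled at day 30 may recover by a different amount over the next 9 weeks than someone enrolled at day 180. Any part of the SPPB change that follows time since transplant then sits in the error term of the treatment comparison unless the model takes it out. With 60 randomised and 20% attrition allowed for, precision is scarce, and this baseline value is already held.

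Model form matters as well. The tested effect is a within-person contrast between arms, so a covariate that shifts only the level of SPPB largely cancels out of it. If the listed covariates enter only as main effects, which the article does not specify, they do little for that test, and days since transplant added in the same way would do no more.

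**Working it through.** **Inputs.** From the article: "We will randomize 60 pre-frail or frail patients with multiple myeloma (1:1"), "there is 20% attrition from baseline to week 9" (so 24 per arm), "60 patients (30 per group) at baseline will achieve 80% power to detect an effect size of at least 0.40 at week 9", a within-person correlation ρ of at least 0.8, and "We will use a two-sided type I error=0.05". Power calculations also gives an SPPB SD of 2.7 and a 1-point target. Not in the documents: r, the within-arm correlation between days since transplant and SPPB change. I take r = 0, 0.2 and 0.4, with 0.6 as an outer value.

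**Step 1: the plan's own figure.** In SD units, for the change from baseline:
- SD of change = √(2(1−ρ)) = √0.4 = 0.632
- SE = 0.632 × √(2/24) = 0.1826
- power = Φ(0.40/0.1826 − 1.96) = Φ(0.231) = 59.1%

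For the week-9 score adjusted for baseline, the SD is √(1−ρ²) = 0.600, the SE is 0.1732 and power is Φ(0.349) = 63.7%. The stated 80% is not reproduced at ρ = 0.8. That is a separate matter for the power section; here these values serve only as the r = 0 starting point.

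**Step 2: gain from adjustment that acts on change.** The SE is multiplied by √(1−r²). At ρ = 0.8 and 24 per arm:

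| r (assumed) | SE factor | Power, change score | Power, baseline-adjusted |
|---|---|---|---|
| 0 | 1.000 | 59.1% | 63.7% |
| 0.2 | 0.980 | 60.9% | 65.4% |
| 0.4 | 0.917 | 66.7% | 71.2% |
| 0.6 | 0.800 | 78.2% | 82.3% |

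In the last column, r refers to the part of the week-9 score not explained by baseline. The change-score gains are 1.8, 7.6 and 19.1 points. At ρ = 0.70, which the article also mentions, power goes from 43.2% to 44.7% (r = 0.2) and 49.7% (r = 0.4). At ρ = 0.9 it goes from 87.3% to 88.5% and 92.2%. The step from 59.1% to 63.7% at r = 0 comes from conditioning on baseline SPPB and owes nothing to days since transplant.

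**Step 3: does the form matter?** A GEE with exchangeable correlation was simulated, 600 runs per scenario, at r = 0.4. The mean SE of the treatment-by-time term was:

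| Data | Days omitted | Main effect only | Days-by-time term |
|---|---|---|---|
| Complete, 30 per arm | 0.1595 | 0.1595 | 0.1464 |
| 20% dropout | 0.1767 | 0.1779 | 0.1625 |

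The main effect gives no gain. The days-by-time term lowers the mean SE by 1 − 0.1464/0.1595 = 8.2% with complete data and 8.0% with dropout. With dropout, the spread of the simulated estimates fell less, from 0.1842 to 0.1766 (4.1%). At r = 0.2 with dropout it did not fall (0.1715 against 0.1720).

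**Step 4: size of a chance imbalance.** If entry is uniform over the window (assumed), the SD is 150/√12 = 43.3 days. The SE of the between-arm difference is 43.3 × √(2/24) = 12.5 days, or 0.29 SD. With SD 2.7 and ρ = 0.8, the SD of change is 2.7 × 0.632 = 1.71 points. A one-SE imbalance shifts the treatment difference by r × 1.71 × 0.289, which is 0.10 points at r = 0.2 and 0.20 at r = 0.4, against the 1-point target.

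**Step 5: cost if unrelated.** With 48 evaluable patients, one more coefficient inflates the variance by roughly 1/45, about 2%, or about 1% in the SE. Break-even is near r² = 0.02, so r is about 0.15.

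**The case against.** The strongest reply is that the article prespecifies three covariates, applies them consistently and contradicts nothing, so asking for a fourth is a preference. It adds that no passage links days since transplant to SPPB or its change. The article gives no recovery trajectory and elsewhere considers decline or mere maintenance. Because entry requires current pre-frailty or frailty, late entrants are those still impaired, which may weaken any link with later recovery. A linear term would also capture less if recovery is steep early and then flat.

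Most of this stands. It rules out calling the omission an error, and it means the range must start at zero. It does not remove the suggestion: the covariate list is stated rather than left open, the article's own account of the cause of dysfunction makes the variable plausible, and the downside is small.

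A reader might infer three stronger things that the documents do not support:
- That the omission biases the result, or that an imbalance could be mistaken for a treatment effect. Randomisation prevents systematic bias, the type I error of the unadjusted test already allows for chance imbalance, and the shift in Step 4 is small against the target.
- That absence from the list is by itself what leaves variance in the error term. Step 3 shows that adding a main effect would change nothing.
- That the plan's covariates are main effects. The text says only that they are included in the GEE, and the detail may be in documents not shown.

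**Conclusion.** The point holds as a modest precision opportunity. A baseline variable that is known for every participant and plausibly related to recovery is outside the stated adjustment set. Its value rests wholly on an assumed r: nothing at r = 0, about 2 power points at r = 0.2 and about 8 at r = 0.4, for ρ = 0.8, 24 per arm and effect size 0.40. The simulation with dropout suggests the realised gain could be smaller. These figures concern SPPB only and do not carry over to the frailty proportions.

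It is tempting to read the r = 0.6 row as a repair for the power shortfall in Step 1. Nothing in the documents supports so strong an association, and the shortfall neither proves that this covariate matters nor is solved by it.

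**What to change.** Before unblinded analysis, prespecify days since transplant at baseline, as a continuous variable, for the SPPB analyses at weeks 9 and 17. Use one of two forms:
- in the repeated-measures model, with a visit interaction; or
- beside baseline SPPB in a covariance-type model of the week-9 and week-17 scores.

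State at the same time whether body mass index, age and race enter with a visit interaction or as main effects only.

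The cost is about one degree of freedom per visit, from data already held, and roughly 1% in the SE if the variable proves unrelated to change. The second form uses post-baseline scores as outcomes, so the plan should say how participants with neither score are handled under its intention-to-treat statement. If the covariate is added only after results are seen, it should be reported as a post hoc sensitivity analysis.

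### Balance of pre-frail and frail patients is left to unstratified permuted blocks, and frailty category is not a covariate: a precision and conditional-bias cost, clearest for Hypothesis 2

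*Protocol article*

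**What the plan says.** - **Population.** Protocol article, Eligibility: patients enter at two levels, "with the presence of 2/5 indices classified as pre-frail and ≥3/5 indices classified as frail". The same section says that "patients who are frail generally have worse outcomes than those who are not", naming survival and treatment discontinuation. It also suggests that pre-frail patients may be the better target for the intervention.
- **Balance.** The Eligibility section closes the matter with an expectation: "We anticipate that the randomized design of the trial will allow for a balanced allocation of pre-frail and frail study participants" between the arms.
- **Allocation.** Methods/design gives 60 patients, 1:1, 30 per arm. Recruitment/randomization says that allocation is made "using a computer-generated permuted block randomization" and names no stratification factor. It follows the baseline outcome assessment. Frailty is also identified by phone at screening, so the category is known before allocation.
- **Adjustment.** Statistical analysis, Hypothesis 1: "Body mass index, age, and race will be determined through medical records and included in GEE as a priori covariates for adjustment". For Hypothesis 2: "As in hypothesis 1, we will include the same covariates for adjustment in the analysis". Hypothesis 3 repeats this. Frailty category is not listed.

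**The concern.** Permuted blocks keep the number of patients per arm equal. Unless they are run within frailty strata, they do nothing for the frailty mix. The article treats frailty as prognostic and as possibly relevant to response, has it in hand before allocation, and then uses it neither in the allocation nor in the models. BMI is a covariate, but it is only one of the five frailty components, so it captures frailty only in part.

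At stake is how well the effect is estimated in the one trial that is run. If the arms differ in their share of frail patients, and frail patients change at a different rate, part of the observed contrast reflects the mix and not the exercise programme. Even without a gap, an unused prognostic factor leaves variance in the comparison that could be removed.

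**Working it through.** The article gives no figure for frailty imbalance, so there is none to reproduce. The frail share is also not given and is varied as an assumption.

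**1. Size of the chance gap.** Inputs: 30 per arm (Methods/design) and an assumed frail share p. The standard deviation of the between-arm difference in share is √(2p(1−p)/30):
- p = 0.5: √(2 × 0.25/30) = 0.129
- p = 0.3: √(2 × 0.21/30) = 0.118

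A typical chance gap is therefore about 12 to 13 points.

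**2. Probability of a gap of 20 points or more** (6 or more patients out of 30).

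*Number frail random:* two independent Binomial(30, p) counts, summed over all pairs that differ by at least 6.

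| Assumed frail share | P(gap ≥ 20 points) |
|---|---|
| 50% | 15.5% |
| 40% or 60% | 14.7% |
| 30% or 70% | 12.0% |
| 20% or 80% | 7.5% |
| 10% or 90% | 1.8% |

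*Number frail fixed at K of 60:* X, the number frail in one arm, is hypergeometric(60, K, 30), and the event is |2X − K| ≥ 6. For K = 30 this means X ≤ 12 or X ≥ 18, with probability 19.6%. Other values are 18.7% at K = 24, 17.0% at K = 20, 10.4% at K = 12 and 2.4% at K = 6. Odd totals are lower, because the smallest qualifying gap is then 7: about 12% at K = 29.

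A gap of 4 or more patients (4/30 = 13 points) has probability 32-37% for random shares of 30-70%, and 44% at K = 30.

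**3. Effect of blocking.** Simulated unstratified permuted blocks of 4 and 6 (8,000 trials per setting) gave about 11-12% at a 30% or 70% share and 16% at 50%, so blocking gives essentially no protection. With the same blocks run within pre-frail and frail strata, no trial of 8,000 reached 20 points. The largest gap was about 7 points (blocks of 4) or 10 points (blocks of 6).

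**4. Consequence for Hypothesis 2.** The outcome is the proportion of patients who are pre-frail or frail. By eligibility every patient has that status at entry (taking the week-0 assessment to agree with the self-report at screening). The baseline value is then the same for all and cannot carry severity. A patient with 2 indices drops below the pre-frail threshold by losing one; a patient with 3 or more must lose at least two. As an illustration with assumed rates, let 40% of pre-frail and 10% of frail patients leave the category. A 20-point gap then shifts the arm contrast by 0.20 × (0.40 − 0.10) = 0.06, or 6 points, with no exercise effect at all.

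**5. Consequence for SPPB.** The test is the treatment-by-time interaction, with baseline SPPB as a response. A difference in level between frail and pre-frail patients cancels; only a difference in change remains. If change differs by an assumed 0.5 to 2 points between the categories, a 20-point gap shifts the contrast by 0.20 × 0.5 = 0.1 to 0.20 × 2 = 0.4 points. The power section's target is 1 point.

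**6. What a covariate does for SPPB.** With complete data at two times, the interaction estimate is the difference between arms in mean change. A covariate that is constant within a patient enters both times equally and cancels. In one simulated trial with an 18 versus 12 split of frail patients and slower change in the frail, the estimate was 0.7705 (SE 0.2914) both with and without a frailty main effect. It moved to 0.551 once a frailty-by-time term was added. With 20% dropout, the main effect moved it only from 0.811 to 0.8075.

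**The case against.** The strongest case for the plan is that unstratified randomization is legitimate. Over repeated randomizations it neither biases the estimate nor inflates the type I error, and the expectation of balance is true on average. This stands. A reader might infer that the comparison is confounded or the test invalid; the documents do not support that.

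A reader might also take one trial in five as the chance of a 20-point gap. That is the maximum, reached with exactly half the patients frail, and the article gives no share that would justify it.

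For SPPB, the interaction test already removes a baseline level difference. This also stands. The article cites worse survival and more treatment discontinuation in frail patients, not a different 8-week change in SPPB, so the premise for SPPB is only plausible. The planned mixed models with subject-specific intercepts and slopes describe variation between patients. They do not remove a difference in mean change caused by an uneven mix.

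Finally, this is a condensed article, and a full protocol or SAP could name a stratum or a sensitivity analysis. That is possible. But the article itself addresses frailty balance and rests it on the randomized design, and it states its a priori covariates expressly. The point therefore concerns choices that are stated, not details left out.

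**Conclusion.** The point holds as a matter of precision and conditional bias, not validity. At 30 per arm a frailty gap of 20 points or more has a probability of about 12-16% for assumed frail shares of 30-70%, rising to 19.6% only at exactly 30 of 60 and falling outside that range. Balance is thus likely but cannot be relied on.

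The case is strongest for Hypothesis 2, where nothing in the planned model separates the two entry levels apart from the partial information in BMI. For SPPB it is weaker and depends on a different rate of change by frailty category; under the assumed differences the shift is 0.1 to 0.4 points against a 1-point target. The frail share, the exit rates and the differences in SPPB change are assumptions, since the article gives none of them.

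**What to change.** 1. **Frailty outcomes (Hypotheses 2 and 3).** Add baseline frailty category (pre-frail versus frail, or the index count) as a covariate for the week-9 and week-17 outcomes. State whether the category comes from the screening self-report or the week-0 assessment; both precede randomization.
2. **SPPB.** Include baseline frailty category with a frailty-by-time term, or in a week-9 model adjusted for baseline SPPB. A main effect alone is not enough, since it leaves the treatment-by-time estimate unchanged with complete data.
3. **Allocation.** Where still practical, run the permuted blocks for the remaining patients separately within pre-frail and frail strata.
4. **Text.** Drop the sentence in Eligibility that anticipates balance and describe the stratification or adjustment in its place.

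The cost is one or two extra model terms, fixed before anyone sees outcomes by arm, and a two-stratum list, which is a small administrative change during recruitment. If the list cannot be changed, items 1 and 2 still help.
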